## Abstract

**Background:**

Intake of free sugars in the population exceeds recommendations, with the largest source in the diet being sugar-sweetened beverages (SSBs). SSB consumption is linked to adverse health consequences and contributes to health inequalities, given greater consumption amongst the most deprived. One possible intervention is to reduce the available sizes of SSB packaging but there is an absence of evidence that this would reduce consumption. Based on evidence from studies targeting food consumption that people consume less when exposed to smaller package sizes, we hypothesise that presenting SSBs in smaller containers reduces consumption. We are planning a crossover randomised controlled trial to assess the impact of presenting a fixed volume of SSB in different bottle sizes on consumption at home. To reduce the uncertainties related to this trial, we propose a preliminary study to assess the feasibility and acceptability of the recruitment, allocation, measurement, retention and intervention procedures.

**Methods/design:**

Households which purchase at least 2 l of regular cola drinks per week and live in Cambridgeshire, UK will have a set amount of a cola SSB (based on their typical weekly purchasing of cola) delivered to their homes each week by the research team. This total amount of cola will be packaged into bottles of one of four sizes: (i) 1500 ml, (ii) 1000 ml, (iii) 500 ml or (iv) 250 ml. A crossover design will be used in which households will each receive all four of the week-long interventions (the four different bottle sizes) over time, randomised in their order of presentation. Approximately 100 eligible households will be approached to assess the proportion interested in actively participating in the study. Of those interested, 16 will be invited to continue participation.

**Discussion:**

The findings will inform the procedures for a crossover randomised controlled trial assessing the impact of presenting a fixed volume of SSB in different bottle sizes on consumption at home. The findings from such a trial are expected to provide the best estimate to date of the effect of container size on beverage consumption and inform ongoing scientific and policy discussions about the effectiveness of this intervention at reducing population intake of free sugars in beverages.

**Trial registration:**

ISRCTN14964130

## Lay summary

What is known alreadyThe consumption of sugar-sweetened beverages is associated with adverse health consequences, including obesity, metabolic syndrome, diabetes and poor oral health, and health inequalities, given higher consumption amongst those who are more socially deprived.One possible intervention to reduce sugar-sweetened beverage consumption is to reduce the container sizes (i.e. bottles and cans) in which these drinks are presented. However, evidence regarding the effectiveness of this intervention is currently lacking.

What this study will addThe findings of this feasibility study will provide the information needed to finalise the design of a planned crossover randomised controlled trial assessing the impact of bottle size on in-home consumption of sugar-sweetened beverages.

Policy implicationsThe findings of the planned trial will inform policy concerning the use of sizing interventions to reduce consumption of sugar-sweetened beverages to improve population health.

## Background

There is increasing concern that the consumption of free sugars (i.e. all mono- and disaccharides added to foods by the manufacturer, cook or consumer, plus sugars naturally present in honey, syrup and fruit juices [1]) can have serious adverse health consequences. Specifically, the intake of such sugars at high levels leads to weight gain and an increased risk of non-communicable diseases (NCDs) [2] and the development of dental diseases, particularly, dental caries [3, 4]. Such concerns have led the World Health Organization (WHO) to advise limiting the consumption of free sugars to less than 10 % of total daily caloric intake, with reductions below 5 % highlighted as having additional health benefits [5]. However, global intake of free sugars exceeds these recommendations, with the largest source in the diet being sugar-sweetened beverages (SSBs) [6, 7]. SSBs are consumed widely around the world, including in the UK and USA, with carbonated drinks being the predominant product. For example, in 2013, carbonated drinks were purchased by 91 % of households in the UK and USA [8, 9]. Also in 2013, the average consumption of carbonated drinks per person in the UK was 103 l [8] and approximately 170 l in the USA [10].

SSBs contain free sugars, including sucrose, high fructose corn syrup and other energy-containing sweeteners. A 330-ml portion of a carbonated SSB typically contains approximately 35 g (i.e. seven teaspoons) of sugar and provides approximately 140 cal, generally without any nutritional value [11, 12]. In recent decades, consumption of SSBs has increased globally [13]. Given that consumers do not tend to reduce their energy intake to compensate for the additional energy provided by SSBs [14], SSB consumption increases total daily energy intake [15–17], has thus been linked to weight gain and the development of obesity [18–20], metabolic syndrome and diabetes [18, 19, 21], as well as hypertension [22], dental diseases [23], gout [24, 25], non-alcoholic steatohepatitis [26], and is associated with an estimated 180,000 global deaths per year [27]. SSB intake may also contribute to observed inequalities in health outcomes, as it is socially patterned: In high-income countries, heavy consumption and purchasing are more common amongst adults and children of lower socio-economic status [28–31]. In the UK, for example, approximately 25 % of the population of regular SSB consumers live in the most deprived areas (i.e. areas ranked in the most deprived quintile based on their Index of Multiple Deprivation (IMD) scores [32]) compared to 15 % who live in the least deprived areas (i.e. areas ranked in the least deprived quintile based on their IMD scores) [29].

Given the contribution of free sugars, especially from SSBs, to the rise in chronic disease and to health inequalities, curbing their intake has been identified for public health action [5, 33]. Identifying effective interventions is recognised as key to this action. Reducing the size of containers in which SSBs are available is one possible intervention. In the USA, a recent attempt to regulate the size of products in order to reduce their consumption comprised a ban on the sale of sugary drinks larger than 16 oz (473 ml) in many out-of-home settings [34]. The proposal has yet to be approved. In the UK, there are recent examples of companies reducing the portion sizes of sugary drinks as part of their voluntary pledges under the government’s Public Health Responsibility Deal in England (https://responsibilitydeal.dh.gov.uk/about/). This intervention, increasing the availability of smaller portion sizes, has not been evaluated for its impact on beverage consumption or purchasing. In theory, several, often conflicting, mechanisms have been suggested as underlying the impact of the size of products, including beverages, on consumption [35, 36]. One possibility is that people are guided by available external cues and so perceive the amount served to them as representing an appropriate portion size (a norm). They therefore consume less when offered smaller portions and more when offered larger portions [36]. Perception of appropriate portion sizes might in turn be influenced by individuals’ personal and social norms about what constitutes a suitable amount to consume. As larger portions have become more prevalent and normalised, smaller portions might be considered less appropriate [37] and therefore fail to reduce consumption. Contrary to this is the suggestion that smaller sizes might reduce consumption, regardless of whether they are considered a suitable portion, by making additional consumption more effortful [38] or due to people’s tendency to consume a specific number of product units in any one episode of consumption regardless of the unit size (referred to as the ‘unit bias heuristic’) [39].

From the above, it is clear that the theoretical literature on this issue is complex and does not allow for confident predictions to be made regarding the impact of bottle size on the consumption of SSBs. However, a large number of studies have examined the effects of portion and package sizing on the consumption of foodstuffs (such as cereal and snack foods) [35–37], and a recent Cochrane review on this topic found that people consume less food the smaller the package size to which they are exposed [38, 39]. It is unclear whether such findings are generalizable to beverage consumption, as there are no studies, to our knowledge, that examine the effects of manipulating the package size of drinks. The lack of relevant studies is also confirmed by the Cochrane review [38, 39]. Based on the aforementioned finding, however, we hypothesise that presenting SSBs in smaller containers will reduce consumption.

To assess this hypothesis and address the absence of relevant evidence, we are proposing a crossover randomised controlled trial to assess the impact of presenting a fixed volume of sugar-sweetened beverages in different bottle sizes on consumption in homes. The focus of this study is on the size of bottles containing cola, given that cola is the most consumed carbonated drink in the UK [8] and is available in a wide range of container sizes. However, prior to conducting this trial, there is a need to reduce key uncertainties related to its design, including the feasibility and acceptability of delivering the intervention to households and replacing existing SSBs and the feasibility of assessing consumption. There are also uncertainties relating to the specific bottle sizes the trial should focus on. As such, we are initially proposing a preliminary study with the aim of assessing the feasibility and acceptability of the procedures for recruitment, allocation, measurement, retention and intervention delivery of the aforementioned randomised controlled trial.

### Aim and objectives

The aim of the current study is to assess the feasibility and acceptability of conducting a randomised controlled trial of the impact of bottle size on consumption of cola in homes.

The specific objectives of the current study are to describe and assess the following:i.Feasibility of recruiting participants from eligible households into the trial, including estimating the recruitment rateii.Characteristics of recruited households, to judge the likelihood of recruiting a sample varied in potential effect modifiers (i.e. socioeconomic factors)iii.Bottle sizes that are most appropriate for use in the planned trialiv.Feasibility and practicalities associated with delivering the interventionv.Acceptability of the interventionvi.Awareness of the purpose of the interventionvii.Possible effect size, to inform sample size calculations for the planned trialviii.Feasibility and acceptability of the assessment proceduresix.Feasibility of collecting end - point datax.Loss-to-follow up rates

## Methods/design

### Setting

The proposed feasibility and acceptability study will be conducted in a community setting comprising residential households, located in Cambridgeshire, UK, including Cambridge City, South Cambridgeshire and East Cambridgeshire, which have a total population of 363,800.

### Design

We propose to use a crossover design in which general population households will each be exposed to four intervention conditions over time, randomised in their order of presentation. The unit of randomisation is the household. The four conditions will comprise receipt of a given quantity of a carbonated cola sugar-sweetened beverage (SSB), sub-divided into bottles of one of four different sizes (Fig. 1).

**Fig. 1 Fig1:**
[figure not shown]
Flow of participants through the study

A within-subjects, crossover design is being used because of the variability between households, which will vary considerably by size, as well as their social and psychological characteristics. Being able to control for these differences makes a within-subjects crossover design preferable to a between-subjects design. It also maximises statistical power thereby increasing efficiency of research resource in terms of accruing the greatest reduction in uncertainty possible from participating households.

### Participants

Participating households will be of any size or composition. We define households as people who live together, who may or may not be related but who share all or most drink and food within the house. This includes households consisting ofSingle membersCouples (married or cohabitating)Families with school age childrenSingle parents with dependent childrenFamilies with extended family members living in the house (e.g. grandparents)

In line with the characteristics of the population of SSB consumers in the UK [29], 50 % of the recruited households will be from areas of high deprivation, as defined by their Index of Multiple Deprivation (IMD)^1^ [32] score, with areas falling under the fourth and fifth IMD quintile considered highly deprived. Inclusion criteria for participating households are as follows:i.Purchase regular (not low sugar) Coca-Cola**®** or Pepsi Cola**®** at a minimum rate of 2 l a week.ii.Reside in or near to Cambridge, UK, within 10 miles of the research team base.iii.Do not plan to be away from home for longer than 7 days during the study period.

We will recruit one individual from each eligible household to act as a household representative, who will consent to participation in the study for the entire household and provide all necessary data. In order to evaluate recruitment rates, we will initially approach 100 eligible households with the aim of assessing how many would be interested in taking part in the study and how many would complete the run-in period (see ‘Procedure’ section for details). We assume that households completing this period would be likely to continue, completing at least one intervention period. Of the households completing the run-in period and expressing a willingness to continue with the study, we will invite 16 to continue their participation and undergo the intervention periods. If fewer than 16 households complete the run-in period, we will approach additional households.

Households will be identified and recruited through a research agency.

### Intervention

The four conditions will comprise receipt of a given quantity of a carbonated cola sugar-sweetened beverage (SSB), sub-divided into bottles of one of four different sizes:i.1500 ml bottles,ii.1000 ml bottles,iii.500 ml bottles andiv.250 ml bottles.

In any 1-week, households will receive their preference of cola (Coca-Cola**®** or Pepsi Cola**®**) in just one size of bottle, with the number of bottles being determined by the total volume of cola each household receives, which will be fixed across all four intervention periods. This fixed volume will be determined with reference to the volume of cola households purchased during a 2-week baseline period, as assessed by till receipts and by self-report, rounded up to the nearest multiple of 3 l. For example, if households purchased 2 l per week, they will receive 3 l during each intervention period; if they purchased three and a half litres, they will receive 6 l etc. Households purchasing amounts already consisting of a multiple of 3 l will receive this exact amount (e.g. if they purchased 3 l, they will receive 3 l). Volumes consisting of multiples of 3 l are needed to avoid the total quantity varying systematically between intervention periods, thereby confounding the effect of altering the bottle size with volume. During each intervention week, households will be given the opportunity to receive additional deliveries should they want these.

All participating households will receive all interventions according to a pre-specified random order (see ‘Randomisation’ section for details). During the first intervention period, four households will receive cola in each of the intervention bottle sizes, subsequently crossing-over to the other conditions during the remaining three intervention periods, until all households have been exposed to all conditions. All intervention periods will be conducted during school term times, in order to avoid increased consumption during any specific period due to the increased presence of children in the homes. During the intervention periods, a researcher will visit participating households to deliver the total volume of the cola (Coca-Cola**®** or Pepsi Cola**®** depending on their preference) SSB for the forthcoming week. The researcher will remove any existing SSB products that are in the household, with financial compensation provided for any removals. At the end of each week, households will be requested to pay for the SSB drinks they consume at their usual purchasing rate. During the intervention periods, households will be requested to continue to keep all bottles whether the contents are consumed, partially consumed or not consumed. They will be told that the reason for this is to accurately estimate how much they need to pay for their drinks, based on the amount they consumed.

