### Baseline assessments

At enrolment, household representatives (i.e. individuals who are recruited from each household to provide the necessary data) will be asked to give written informed consent on behalf of their household for participating in the study and for adhering to the study procedures. Following this, they will be requested to complete a questionnaire to record their household’s demographic characteristics, including the number of adults and children living in their home, their age, gender, highest educational qualification and annual household income. They will also be asked to indicate how much cola per week their household usually buys for in-home consumption, as well as the total amount their household drinks outside the home. The amount of cola typically consumed per week by each household will also be estimated based on grocery shopping till receipts, which household representatives will be asked to collect during a 2-week period. Discrepancies between amounts indicated by till receipts and self-report will be discussed with household representatives, in order to determine the household’s typical weekly consumption as accurately as possible.

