### Data analysis

The main analysis of this study will include descriptive statistics of feasibility and acceptability outcomes, including recruitment and attrition rates. We will also calculate the average change from baseline in SSB consumption during each intervention period to estimate possible effect sizes from which to power the main trial.

Analysis of the anonymised data gathered through the semi-structured interviews will be conducted following the principles of the Framework method [41].

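### The effect size for the main trial is taken from change against a purchase-based baseline, which can move without any bottle-size effect; it should come from within-household differences between bottle sizes

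*Protocol article*

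**What the plan says.** **Planned statistic.** The Data analysis section states that the team will "calculate the average change from baseline in SSB consumption during each intervention period to estimate possible effect sizes from which to power the main trial". That section names no contrast between bottle sizes. A possible effect size to inform the main trial's sample size is also one of the ten listed objectives.

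**Baseline.** The delivered volume is set from the "volume of cola households purchased during a 2-week baseline period, as assessed by till receipts and by self-report" (Intervention). Under Baseline assessments, the representative is asked "how much cola per week their household usually buys for in-home consumption", and typical weekly consumption "will also be estimated based on grocery shopping till receipts". Discrepancies between the two sources are settled by discussion.

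**Follow-up.** Cola used in each intervention week is measured from empty, full and part-used bottles, and is also self-reported as the amount consumed (Follow-up assessments; Outcomes and measures).

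**Supply during follow-up.** The weekly volume is the baseline purchase "rounded up to the nearest multiple of 3 l"; for example, "if they purchased three and a half litres, they will receive 6 l etc". Exact multiples are delivered unchanged. The volume is the same in all four periods, and households may ask for more. In addition, "The researcher will remove any existing SSB products that are in the household". Households pay at their usual rate for what they consume.

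**The concern.** A change from baseline measures an intervention effect only if the two ends differ in nothing but the intervention. Here three other things differ:

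- **What is measured.** Baseline is what was bought; follow-up is what was used. The self-report route has the same mismatch, because the baseline item asks about buying and the follow-up item asks about consumption.
- **How much is in the house.** The delivery equals or exceeds the purchased amount and is never below it.
- **What else is available.** Other sugar-sweetened drinks are removed, so delivered cola may take their place.

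None of these is caused by bottle size, yet each can move the change from baseline. At stake is the figure handed to the main trial. That trial will ask how much less is drunk from one bottle size than from another. A change against recorded purchases answers a different question. Its standard deviation also contains variation between households, which the Design section says the crossover was chosen to control.

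**Working it through.** **1. The rounding rule.** Delivered = 3 × ceil(purchased / 3); surplus = delivered − purchased. The protocol's examples reproduce:

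| Purchased (l/week) | Delivered (l) | Surplus (l) | Surplus (%) |
|---|---|---|---|
| 2 | 3 | 1.0 | 1/2 = 50 |
| 3 | 3 | 0 | 0 |
| 3.5 | 6 | 2.5 | 2.5/3.5 = 71 |
| 3.01 (added here) | 6 | 2.99 | 2.99/3.01 = 99 |

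The surplus thus runs from zero to just under 3 l. The rule itself is sound: 3 l is the smallest volume that divides exactly into 1500, 1000, 500 and 250 ml bottles (2, 3, 6 and 12 of them).

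**2. Average surplus (assumed distribution).** The protocol gives no distribution of baseline purchases. Assume it uniform from the 2 l eligibility minimum to an upper limit U. Surplus averages 0.5 l over 2–3 l and 1.5 l over each later 3 l band.

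- U = 6: (1 × 0.5 + 3 × 1.5)/4 = 1.25 l; against a mean purchase of 4 l, 31%.
- U = 9: (1 × 0.5 + 6 × 1.5)/7 = 1.36 l; against 5.5 l, 25%.
- U = 12: (1 × 0.5 + 9 × 1.5)/10 = 1.40 l; against 7 l, 20%.

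If purchases fall on half-litre steps, the means drop to 1.0, 1.10 and 1.14 l, and about a fifth of values (19–22%) have no surplus.

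**3. Change from baseline when bottle size does nothing.** Let use = m × purchased + f × surplus + noise. Here m is the ratio of measured use to recorded purchase, and f is the share of the surplus that is drunk. Neither is in the protocol. Mean change = (m − 1) × mean purchase + f × mean surplus. With U = 9:

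| m | f | Mean change (l/week) |
|---|---|---|
| 1.0 | 0 | 0 |
| 1.0 | 0.25 | 0.25 × 1.36 = +0.34 |
| 1.0 | 0.5 | +0.68 |
| 1.0 | 1 | +1.36 |
| 0.9 | 0 | −0.1 × 5.5 = −0.55 |
| 1.1 | 0 | +0.55 |
| 0.9 | 0.25 | −0.55 + 0.34 = −0.21 |

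The value is the same in all four conditions. Both signs, and zero, are possible.

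**4. The contrast between sizes.** Each household has one baseline B. For sizes j and k, (Cj − B) − (Ck − B) = Cj − Ck, so baseline drops out, and so does any shift common to the household's four weeks. A simulation of the model in step 3 (200,000 households, noise SD 0.5 l) kept this contrast within 0.004 l of zero for every combination of m = 0.9, 1.0, 1.1 and f = 0, 0.25, 0.5, 1.

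**5. Spread.** With U = 9, the mean squared surplus is (1 × 1/3 + 6 × 3)/7 = 2.619. The variance is 2.619 − 1.357² = 0.777, so the SD is 0.88 l. With m = 1 and the same noise SD of 0.5 l:

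- SD of change from baseline = √(0.777 f² + 0.25): 0.50, 0.67 and 1.01 l for f = 0, 0.5 and 1.
- SD of the within-household difference = √2 × 0.5 = 0.71 l, whatever f is.

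The first can lie below or above the second, so the direction of any mis-sizing cannot be predicted.

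**The case against.** The strongest reply is that the shift cancels. One baseline is subtracted from all four weeks, so with complete data the difference between two sizes' mean changes is exactly the within-household contrast. This is correct and it limits the point. A reader might infer that the randomised comparison is biased, or that a size that truly lowers consumption relative to another could appear to raise it. The documents do not support that: delivered volume is fixed across periods, and only the level against baseline is affected. The reply does not rescue the stated statistic, though, because the Data analysis section draws effect sizes from the change itself. Read literally, a period average also mixes all four sizes, since Table 1 places four households on each size in every period.

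Other replies carry weight:

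- **Payment.** Households pay for what they consume, which may discourage drinking the surplus. This may limit the shift but does not measure or remove it.
- **Baseline quality.** Receipts and self-report are reconciled to approximate typical consumption. That helps, but both sources still record buying.
- **Feasibility status.** No power calculation is needed here, the main analysis is descriptive, and none of the four listed success criteria uses an effect size. This lowers the severity.
- **Terminology.** The product is defined as a cola sugar-sweetened beverage, and the outcome list names cola volume. The looser label in the Data analysis section is a minor matter.

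Two further inferences should not be drawn. Not every household is oversupplied, because exact multiples of 3 l are delivered as they are. Regression to the mean from the 2 l entry criterion is not shown either, since the protocol does not say that selection rests on the same record as the baseline.

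**Conclusion.** The point holds, with moderate severity. The planned source of the main trial's effect size can be non-zero with no bottle-size effect, and its between-household spread is not the variability on which a crossover comparison is sized. The documented part is the mismatch between bought and used, and the oversupply of 50% and 71% in the protocol's own examples. Oversupply is not itself bias. The litre figures (for instance +0.34 l/week if a quarter of the surplus is drunk) rest on an assumed uniform distribution and an assumed share; they show what is possible and do not estimate the bias. Comparisons between bottle sizes are unaffected as long as the shift is common to a household's four weeks, which the fixed volume is designed to secure.

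**What to change.** Amend the Data analysis section in three respects:

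1. Take the possible effect size, and its standard deviation, from within-household differences in measured cola volume between bottle sizes. Index them by bottle size, not by period.
2. Keep change from baseline as a descriptive summary only, with a note that baseline is purchase-based and deliveries may exceed it.
3. Call the outcome cola volume, as the Outcomes and measures section does.

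The 3 l rule should stay, because it equalises volume across sizes. The run-in week is not a good substitute reference: households then receive mixed sizes to drink freely, the article gives no volume for that week, and removal of existing drinks is described only for the intervention periods.

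The cost is a few sentences. The bottle measurements are already planned for every intervention week, so no extra data or visits are needed.

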### Procedure

Participation will comprise seven stages:Two-week recruitment and baseline assessment period (see ‘Baseline assessments’ section for details).One-week run-in period. Households will receive a range of differently sized bottled drinks to store in their homes to consume freely. This period functions to acquaint them with both the idea that a wide range of bottle sizes is available and that drinks will be delivered to them over the course of the study. More generally, it will build credibility of the study as a consumer research exercise. Study randomisation will be conducted during this period.First intervention period: 1 week in duration.Second intervention period: 1 week in duration.Third intervention period: 1 week in duration.Fourth intervention period: 1 week in duration.End of study and debriefing.

Stages 1–2 will be completed by any number of eligible households out of the 100 approached that agree to do so.

Stages 3–7 will be completed by 16 households, randomly selected from those completing stages 1–2, who also express a willingness to continue participation in the study. If only 16 households agree to continue their participation, all will be invited to complete these additional stages.

Each household will receive £150 worth of shopping vouchers at the end of the study for completion of all intervention periods and follow-up assessments. This amount was determined based on the national minimum wage rates per hour and the level of commitment and amount of time spent participating in the study (approximately 25 h during 5-week period). Households completing the run-in period but not invited to continue their participation, or not interested in continuing, will receive £30 worth of shopping vouchers.

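### The term-time rule leaves out the 2-week baseline, so change from baseline can carry a school-holiday artefact common to all four bottle sizes

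*Protocol article*

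**What the plan says.** The Intervention section restricts the calendar for one part of the study only, and gives its reason: "All intervention periods will be conducted during school term times, in order to avoid increased consumption during any specific period". The increase it has in mind is the one caused by more children being at home.

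The Procedure section places two stages before the intervention weeks, a "Two-week recruitment and baseline assessment period" and a "One-week run-in period". Neither has a calendar limit.

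The baseline is used twice:

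- **Delivered volume** (Intervention section): "This fixed volume will be determined with reference to the volume of cola households purchased during a 2-week baseline period". The amount comes from till receipts and self-report, is rounded up to a multiple of 3 l, and stays the same in all four weeks.
- **Effect size** (Data analysis section): the authors will "calculate the average change from baseline in SSB consumption during each intervention period" and use the result to power the main trial. This serves objective vii.

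The Baseline assessments section adds a safeguard. The representative reports how much cola the household usually buys, and any disagreement with the receipts is talked through to settle on a typical weekly amount. The section does not say whether a typical week means a school week.

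**The concern.** The protocol itself accepts that consumption goes up when children are at home, and it protects the four intervention weeks for that reason. This makes those weeks comparable with one another. It does not make them comparable with the baseline, and change from baseline is the only effect measure that the Data analysis section names.

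Families with school-age children are among the households listed as eligible. If their baseline falls in a holiday and their intervention weeks in term, a return to ordinary school-week use is recorded as a change from baseline under every bottle size. That change would enter the figures carried forward to the main trial. The same baseline can also raise the fixed volume delivered in all four weeks. Receipts gathered in a holiday cannot be turned into term-time receipts afterwards, so the point has to be settled in the schedule.

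**Working it through.** **Inputs from the protocol article.** Baseline 2 weeks, run-in 1 week, four 1-week intervention periods (Procedure). Volume rounded up to a multiple of 3 l (Intervention). Effect measure: change from baseline (Data analysis).

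**Assumptions.** The documents give no holiday rise, so *h* = 10%, 20% and 30% are used. *w* is the share of the two baseline weeks in holiday (0.5 or 1). *r* is the weight given to receipts against a usual-week report that reflects term time (1 = receipts only, 0.5 = the two averaged, 0 = usual week only). Intake is taken as unaffected by the amount delivered.

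**1. The plan's own figures.** Delivered volume = 3 × ceil(V/3). For V = 2, 3 and 3.5 l this gives 3, 3 and 6 l. These match the examples given, including "if they purchased three and a half litres, they will receive 6 l etc". There is no power figure to reproduce.

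**2. Can a compliant schedule put baseline in a holiday?** With consecutive stages, if the first intervention week is term week *t*, the run-in is week *t* − 1 and baseline is weeks *t* − 3 and *t* − 2. After a holiday of at least 3 weeks:

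- *t* = 1: baseline is weeks −2 and −1, both before term.
- *t* = 2: weeks −1 and 0, both before term.
- *t* = 3: weeks 0 and 1, one before term.
- *t* = 4: weeks 1 and 2, none before term.

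So a start in any of the first three weeks of term obeys the rule and still exposes the baseline.

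**3. False change with no true effect.** Set term-time use to 1. The recorded baseline is 1 + *h·w·r*, so the false change is 1/(1 + *h·w·r*) − 1.

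| Baseline source | Holiday weeks | h = 10% | h = 20% | h = 30% |
|---|---|---|---|---|
| Receipts only (r = 1) | both | −9.1% | −16.7% | −23.1% |
| Receipts only (r = 1) | one | −4.8% | −9.1% | −13.0% |
| Averaged (r = 0.5) | both | −4.8% | −9.1% | −13.0% |
| Averaged (r = 0.5) | one | −2.4% | −4.8% | −7.0% |
| Usual term-time week (r = 0) | either | 0% | 0% | 0% |

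For example, receipts only, both weeks, *h* = 30%: 1/1.30 − 1 = −23.1%. These figures are per affected household. The average over 16 households is diluted by those not affected.

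**4. Delivered volume, receipts only, both weeks in holiday.**

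| Term-time purchase | Delivered on that amount | Delivered at h = 20% |
|---|---|---|
| 2 l | 3 l | 3 l (2.4 l) |
| 2.8 l | 3 l | 6 l (3.36 l) |
| 3.5 l | 6 l | 6 l (4.2 l) |
| 5.5 l | 6 l | 9 l (6.6 l) |

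The delivery changes only when the rise carries the household across a 3 l boundary.

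**5. Comparisons between sizes.** Each household has one baseline B. For sizes *s* and *u*, (C_s − B) − (C_u − B) = C_s − C_u, so B cancels. In 16 simulated households using 2 to 8 l a week, a 20% inflated baseline moved the mean change by −1.02 l under every size. With true reductions of 10% and 5% put in for two of the sizes, their differences from an unaffected size were −0.51 l and −0.255 l with or without the inflation. Expressed as a percentage of the inflated baseline, the 10-point difference shrinks to 25.0 − 16.7 = 8.3 points. The differences in millilitres are exact.

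**6. With baseline in term time.** *w* = 0, so the false change is 0% for every *h*.

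**The case against.** The strongest reply is that the protocol does not rely on the two baseline weeks alone. The representative is asked about usual purchasing, and differences from the receipts are resolved towards a typical week. This stands in large part: it could catch much of a holiday excess and, at best, bring the false change to 0%. It does not close the gap, because a typical week is not defined as a term-time week and nothing requires the usual-week report to override the receipts.

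Second, the rule has a narrower purpose, which is to stop one intervention week being inflated relative to another. It achieves that, so the protocol does not contradict itself.

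Third, a reader might infer that the artefact favours the hypothesis that smaller bottles reduce consumption. The documents do not support this. The baseline and the delivered volume are common to all four sizes within a household, so 1500 ml is shifted as much as 250 ml. Nor is a net fall certain: a household moved from 3 l to 6 l has more cola at home and might drink more.

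Fourth, a reader might infer that families in general would have their supply doubled. That also fails. A 2 l household stays at 3 l and a 3.5 l household at 6 l across the assumed 10–30% rise.

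Finally, nothing schedules baseline in a holiday, the study has 16 households and a mainly descriptive analysis, and none of the success criteria in the Discussion uses the effect size. All of this is true, and it limits the weight of the point.

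**Conclusion.** The point holds in a limited form and is a minor, inexpensive improvement. The term-time rule leaves out the period that informs the delivered volume and is the comparator for the stated effect measure, so a compliant schedule can mix season with intervention in the change from baseline.

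The size depends on a holiday rise that the documents do not give and on how receipts and usual purchasing are reconciled. For a 10–30% rise, and intake unaffected by stock, the false fall in an affected household lies anywhere from 0% to 23.1%. The top of that range, 9.1–23.1%, needs both baseline weeks in holiday and no correction from the usual-week report, so it is a worst case and not an expected value.

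The point concerns households with school-age children whose intervention weeks begin soon after a holiday. It affects the absolute change for each size, not the differences between sizes in millilitres.

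**What to change.** Three small changes:

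1. Extend the term-time sentence in the Intervention section so that the 2-week baseline is also collected in school term.
2. In the Baseline assessments section, define the typical weekly amount as that of a term-time week, so that the discussion of discrepancies has a fixed target.
3. In the Data analysis section, base the effect size for the main trial on within-household differences between bottle sizes, in millilitres, as well as on change from baseline.

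The first costs tighter scheduling. Baseline, run-in and intervention take 2 + 1 + 4 = 7 weeks, and where these do not fit in one stretch of term, some households will start later or have a gap between baseline and the first intervention week. A long gap makes the baseline less current, so it should be kept short and recorded. The second and third need only a change of wording. None of the three adds households, visits or measurements.
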